### 3.1.3 Cluster-Randomized Trial:

This **cluster-randomized trial** will use a longitudinal pre-post research design. Data will be collected from two groups (1 intervention and 1 control) with three comparisons. The groups will be comprised of primary care outpatient clinics within the UNC HealthCare System, including family medicine, primary care, and geriatric clinics. Clinics will be randomly selected into either intervention or control clinics. Study team members will work with providers at intervention clinics to implement the educational intervention, which is designed to reduce falls risk through opioid and BZD deprescribing. Potentially eligible patients will be shared with physicians at intervention clinics. Emphasis will be placed on this list as a potential list; in no way are the study team mandating providers to de-prescribe opioids or BZDs in these patients. The decision to de-prescribe is left solely to the provider.

## 3.2 Study Duration, Enrollment and Number of Subjects

This study will last for 4 total years. Year 1 will consist of organizing the study team and conducting focus groups. In Year 2, clinics will be randomized, and the educational intervention will be finalized for testing. The cluster-randomized intervention will begin in the 7th month of year 2 and last through the 6th month of year 3. Data analysis will be conducted in the remainder of year 3 and into year 4.

We expect the following number of participants:

- Focus Groups: 12 patients, 12 providers
- Web-based surveys: 120 providers
- Cluster-randomized trial:
  - Number of clinics (intervention & control): 20;
  - Number of patients (intervention and control): 3,000

## 3.3 Study Population

**Inclusion Criteria:** To be eligible to participate in the study, clinics need to be affiliated with UNC HealthCare and have a patient population that includes patients 65 years of age or older. Targeted patients will be ambulatory (not institutionalized), aged at least 65 years old and taking at least one opioid or benzodiazepine medication listed in the design section for > 6 weeks, indicating they are at high risk for falls.

The UNC HealthCare outpatient clinics serve a diverse patient population, including women and minorities. The patient population served varies across clinics and geographical areas. UNC HealthCare coordinates care and manages care for more than 130,000 older adult patients in North Carolina. These beneficiaries are from all over the state. Females comprise 65.5% of the population. Approximately 52% are White, Non-Hispanic, 5.0% are Hispanic, 3.0% are Native American, 2.0% are Asian, and 38% are African American, Non-Hispanic.

To be eligible to participate in the patient focus group, participants need to be a patient in one of the intervention group clinics, 65 years of age and older, and taking at least one opioid or benzodiazepine chronically.

#### **Exclusion Criteria:**

Clinics that do not provide primary care services will be excluded from participating in the study.

Patients will be excluded from the focus groups if they are not English speaking, exhibit signs of cognitive impairment or speech/hearing deficits, are undergoing active cancer treatment, receiving hospice care, live in a skilled nursing facility, or do not wish to be audio-recorded.

Patients will be excluded from the cluster-randomized trial analysis if their EHR problem list indicates they have cancer, cognitive impairment, are receiving hospice care, live in a skilled nursing facility, or are non-English speaking.

## **4 STUDY PROCEDURES (what will be done)**

### **4.1 Screening/Baseline Visit Procedures and Observation Procedures for the Focus Groups:**

- (1) Patient Focus Groups:** We will conduct one focus group with 12 patients who are active users of opioids and/or BZDs prior to the implementation of the intervention. Patients will be recruited from intervention clinics. The focus group will be recorded and transcribed, data will be analyzed as described in Section 3.1.1. Results from the focus group will inform the design of the toolkit's patient education resources to support the deprescribing intervention.
- (2) Provider Focus Groups:** We will conduct one focus group with 12 healthcare providers who are actively engaged in treatment of patients who are taking opioids and BZDs. Providers will also be recruited from intervention clinics. The focus group will be recorded and transcribed, and data will be analyzed as described in Section 3.1.1. Results from the focus group will inform the design of the toolkit and associated resources to support the deprescribing intervention.

### **4.2 Screening/Baseline Visit Procedures and Observation Procedures for the Cluster-Randomized Trial:**

- (1) Randomize intervention and control clinics:** A list of clinics that are interested in participating will be compiled by the primary investigators. A member of the study team, [name], PhD, will use the random number generator built into SAS to randomize 10 clinics into treatment and 10 clinics into control groups. If the number of potentially eligible clinics exceeds 20, 20 clinics will be chosen at random, and this list will subsequently be divided into 10 random treatment clinics and 10 random controls. Results of randomization will be provided to the study coordinators, who will inform clinics of their status.

Data for all patients who meet inclusion criteria will be included in this analysis. This educational

intervention is intended to better inform providers in intervention clinics as to the fall-related risks associated with opioids and BZDs as well as best practices in deprescribing opioids and BZDs. A toolkit to support screening and deprescribing will also be provided to providers at intervention clinics. It is expected that providers will use this information to attempt deprescribing for any patients for whom they feel the benefits of deprescribing outweigh the risks. The study team will collect data from the EHR on all potentially eligible patients, regardless of any attempted deprescribing. The same data will be collected for patients who received care from treatment and control clinics.

**(2) Screen for risk of falling:** Intervention group clinics will be expected to screen all patients who appear on the baseline report for falls risk, questions if the patient has not already been screened previously, by using the STEADI screening questions. Each clinic will be allowed to determine how they will integrate these questions into the patient care process. Although the processes used to integrate the screening questions into patient care will vary across clinics, all clinics will be required to enter patient responses to the questions into the EHR, as is standard practice in all UNC HealthCare clinics.

**(3) Educate about opioid and BZD medications as they relate to falls:** Intervention Group clinics will be encouraged to educate all patients who appear on the baseline report for opioid and BZD use that may place them at increased risk for falls. The baseline report will include all patients in that clinic who are 65 years and older and on an opioid and/or BZD for > 6 weeks. Printed and online educational materials highlighting the risks associated with opioid and BZD use will be provided to clinics for their patients. Providers will be encouraged to use these materials in conjunction with verbal education.

**(4) Educate on overall fall prevention strategies:** Printed and online patient education materials regarding falls risk and falls prevention will be given to the intervention clinics to give to patients whom they believe would benefit from the materials. General patient education materials, not specific to opioids or benzodiazepines, will be given to all control clinics.

**(5) Implement the Deprescribing Educational Intervention:** A medication review is part of usual care conducted during a typical clinic visit. If utilized, the toolkit and associated resources can augment this process. During the medication review, the HCP (e.g. nurse, physician, pharmacist, etc.) will follow a consistent approach to patient care, reviewing the patient's medications and identifying medication therapy problems. Special attention will be given to the opioid and BZD medications that the patient is taking since these medications are the focus of this project. To improve the process of the deprescribing for opioids and BZDs, a guidance algorithm and deprescribing toolkit will be available for use. The deprescribing toolkit is being developed by the research team and is based upon evidence-based literature and clinical guidelines. For this study, we will use the toolkit to offer suggestions of medications that may assist with pain and sleep as alternatives to opioids and BZDs. We will also provide patient education materials for the clinics to give their patients. We will make revisions to the toolkit based on feedback from our provider focus group and will amend or supplement our patient education resources based on feedback from our patient focus group.

HCPs performing the opioid and BZD medication reviews will be trained by research personnel (see *Training of Personnel*) to use the toolkit to guide the assessment of opioid and BZD use, the assessment of the patient's risk of falls, and the development of recommendations including possible non-pharmacological interventions they can introduce. In all cases, however, the HCPs will be trained to use their clinical judgment and weigh the risk versus benefit of a medication change before making a recommendation. If the need for a reduction in opioid or BZD dose is warranted, the reasoning and potential solutions will be discussed with the patient. As part of this discussion, the HCP will assess patient willingness to make recommended changes to their medication regimen. As appropriate, patient preferences will be incorporated into recommendations implemented. Patients will receive follow-up from the clinic within a timeframe that fits with the deprescribing strategy employed and which the provider and patient agree upon. During the assessment phase, the provider will also solicit information from the patient concerning medical problems associated with an increased risk of falls (e.g., orthostatic hypotension, nocturia) and provide fall prevention education based on the STEADI resources provided in the toolkit.

**(6) Training of Personnel.** All personnel at Intervention Group clinics will be required to take part in an educational training session, which will include information about the study's purpose, general processes, and available resources. The training session will include physicians, physician assistants, nurse practitioners, nurses, pharmacists, technicians, medical assistants, office managers, case managers and quality improvement officers. Following the training, clinic staff will be able to (1) administer the three STEADI screening questions to all older adults identified in the baseline reports generated by Epic EHR data; (2) identify patients who qualify for the deprescribing intervention; (3) provide patients education about the risks associated with opioid use, BZD use, and falls; and (4) utilize the toolkit and associated resources to effectively and safely deprescribe opioids and BZDs when warranted. Special emphasis will be placed on sharing non-pharmacological recommendations with patients as alternatives to medications associated with an increased risk of falling. Finally, we also will provide in the toolkit - for clinicians interested in learning more - primary literature and other resources related to deprescribing.

**(7)** Following launch of the study, continuous quality improvement processes will be initiated. Specifically, a postdoctoral fellow based in the central project office will contact each intervention clinic within one week of the implementation of the intervention, then monthly thereafter. The phone contact will enable clinic personnel to: (1) ask and have answered any questions they may have about study procedures and (2) report unforeseen issues that need to be addressed, including safety concerns related to deprescribing. The fellow will also conduct clinic site visits if needed to resolve unforeseen problems and maintain engagement and fidelity for the duration of the project.

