| Study Duration                                         | Focus groups: two focus groups (120 minutes each)
Web-based survey: 1 survey, given twice: pre-study and post-study
Cluster-randomized trial: 1 year
The entire study is expected to last 4 years                                                                                                                                                                                                                   |
| Study Phases
Screening
Observation | Focus groups: Participants will sign a consent form prior to the start of the focus group session.
Web-based surveys: The surveys will include a written statement stating that their participation in the survey is voluntary and by completing the survey they are consenting to participate.
Cluster-Randomized Trial: Each clinic's 'study champion' will sign a consent form prior to the clinic's participation. |
| Safety Evaluations                                     | The risk from focus groups and web-based surveys is expected to be minimal. To monitor safety from the educational intervention, we                                                                                                                                                                                                                                                                                                               |

---

---

will include specific monitoring criteria in the educational intervention itself (e.g., monthly follow-up with clinic champions about the study), with specific instructions to alert study staff if any adverse effects of deprescribing are observed. Additionally, a study team member will reach out to all intervention clinics monthly to ask about potential safety risks related to deprescribing.

---

---

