#### **4.3 Subject Completion/ Withdrawal procedures**

Any clinic wishing to withdraw from the intervention group can do so at any time.

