### 6.3 Statistical Methods

**Primary Analyses:** We will examine between-group differences in opioid and BZD exposure associated with an increased risk of falls in the intervention and control groups. Analyses will be performed using the following intention-to-treat principle, and index dates for the intervention group will correspond to the date on which they first received any intervention-related clinical activity. Index dates for otherwise eligible patients from the control group will be chosen at random from each patients' set of clinic visits corresponding to an eligible intervention visit during the study period. Our primary hypotheses are:

- Relative to individuals in both control groups, individuals in both intervention groups will experience a significant reduction in the milligram equivalent exposure to opioids and BZDs during the 1-year follow-up period.

- Relative to individuals in both control groups, individuals in both intervention groups will experience a significantly greater discontinuation rate of opioids and BZDs during the follow-up period 181 to 360 days after index.

There are two overlapping groups of patients aged 65+ that will be included in this study: opioid users and BZD users. For each hypothesis, there will be separate models comparing the impact of the program on opioid users and BZD users. Patients who use both will appear in both models. To examine any differential impact of the program among patients who use both classes of medications, a sensitivity analysis will be performed and will include an indicator variable for patients who use both classes.

Generalized estimating equations (GEE, PROC GENMOD) will be used to create longitudinal pre-post model for the milligram equivalent exposure models. An identity link with a normal distribution will be used for milligram equivalent exposure. The functional form of the model is as follows:

$$\text{Eq. 1: } Y = \beta_0 + \beta_1 X_{\text{exp}} + \beta_2 X_{\text{period}} + \beta_3 X_{\text{exp} \times \text{period}} + \beta_n X_n + \epsilon$$

Where  $X_{\text{exp}}$  is the exposure group indicator,  $X_{\text{period}}$  is the pre-post indicator, and  $X_{\text{exp} \times \text{period}}$  is the period-by-treatment interaction indicator and, correspondingly,  $\beta_3$  is the parameter of the difference in outcome by period for the intervention group compared to the control.  $X_n$  represents a vector of covariates.

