## 10 CONSENT PROCESS

Clinics: [name], with other team members from the UNC Medical School, will reach out to key stakeholders in the targeted clinics (practice managers and/or physicians). They will provide a letter of invitation to participate in the study and will meet with these key stakeholders in person to discuss any questions the stakeholders have about the nature of the study, procedures, risks, and benefits. A copy of the study's IRB application will be provided to these stakeholders if requested. Each clinic's 'study champion' will be asked to sign a consent form prior to the clinic's participation. Consent from clinic patients will not need to be obtained since the study's intervention will be focused on educating providers on improving their delivery of the standard of care.

Providers in participating clinics, who will be asked to complete two web-based surveys, will be provided a written consent form that they will need to submit electronically prior to being able to access the survey questions. This consent form will include a written statement stating that their participation in the survey is voluntary and by completing the survey they are consenting to participate. The consent form will also delineate the nature of the study and the risks and benefits of participating.

Focus group participants will be provided a written consent form that they will need to sign prior to the start of the focus group session. The consent forms will delineate the nature of the study and the risks and benefits of participating in the focus group.

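### Clinics are randomised on expressed interest and told their arm, and the only exit rule is for the intervention group, so one-sided exit after allocation is possible and the intention-to-treat analysis cannot fully absorb it

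*Protocol*

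**What the plan says.** Section 4.2(1) of the protocol gives the sequence. First, "A list of clinics that are interested in participating will be compiled by the primary investigators". Next, the SAS random number generator is used to "randomize 10 clinics into treatment and 10 clinics into control groups", after a random draw of 20 if more than 20 are eligible. Then: "Results of randomization will be provided to the study coordinators, who will inform clinics of their status".

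Clinic consent appears in two places. Section 10 says "Each clinic's 'study champion' will be asked to sign a consent form prior to the clinic's participation", and the Study Phases row of the synopsis says "Each clinic's 'study champion' will sign a consent form prior to the clinic's participation". Neither ties the signature to randomisation or to disclosure of the arm.

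Section 4.3 is one sentence: "Any clinic wishing to withdraw from the intervention group can do so at any time". Nothing is said about control clinics, about the data of a clinic that leaves, or about replacement.

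Two statements bear on how such clinics would be analysed. Section 4.2(1) says "The study team will collect data from the EHR on all potentially eligible patients, regardless of any attempted deprescribing", and that everyone meeting the inclusion criteria is analysed. Section 6.3 says "Analyses will be performed using the following intention-to-treat principle". The same sentence of Section 6.3 dates each intervention patient from the first intervention-related activity received. Control patients get a randomly chosen visit.

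**The concern.** The two arms ask very different things of a clinic. Section 4.2 requires all intervention personnel to attend training, expects screening of every patient on the baseline report, and adds a call within a week of launch and then monthly. Control clinics receive general education materials. Allocation is open. A clinic lukewarm about deprescribing has a reason to step back if drawn to the intervention arm and little reason to do so if drawn to control.

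Willingness to deprescribe is closely related to the primary outcomes of dose and discontinuation. With 10 clinics per arm, each clinic is a tenth of its arm. One or two arm-related exits would either remove part of the randomised comparison or dilute the effect, depending on how those clinics are analysed. The handling therefore needs to be fixed before allocation is revealed.

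**Working it through.** **Step 1. Order of events.** Setting Sections 4.2(1), 10 and 4.3 side by side:

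- Entry to the randomisation list: interest only.
- Disclosure of arm: directly after randomisation.
- Signature: before participation, a term the protocol does not define. It could be before or after randomisation.
- Exit: at any time, worded for the intervention group.

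Whatever the timing of the signature, Section 4.3 permits exit after disclosure. If the signature comes after disclosure, a clinic may also never sign.

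**Step 2. Can a departed clinic's patients be analysed as allocated?** The dose outcome needs 12 months before and after the index date; discontinuation needs days 181 to 360 after it (Section 5). Under Section 6.3 an intervention patient's index date is the first intervention activity. If the clinic leaves before starting, that date does not exist, so neither outcome window can be placed. The data may sit in the EHR, but the analysis has no rule for using them.

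**Step 3. Size if lost clinics are dropped.** The protocol gives no figure to reproduce. Assumptions: comparison of clinic means, normal approximation, no true effect, and *k* of 10 intervention clinics lost whose change averages *d* between-clinic SDs below the arm mean. Neither *k* nor *d* is in the protocol.

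- Shift = k·d/(10 − k)
- SE = √(1/(10 − k) + 1/10)
- Type I error = P(|Z + shift/SE| > 1.96)

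| k | d | Shift | SE | Type I error |
|---|---|---|---|---|
| 1 | 1 | 0.111 | 0.459 | 0.057 |
| 2 | 1 | 0.250 | 0.474 | 0.082 |
| 2 | 1.5 | 0.375 | 0.474 | 0.124 |
| 3 | 1 | 0.429 | 0.493 | 0.140 |

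**Step 4. Size if they are kept and show no effect.** From Section 6.4.1: difference 0.30, correlation 0.2, 20% attrition, so 3000 × 0.8 / 2 = 1200 per arm. The SD of 2 is chosen from the stated range of 1 to 3. For the period-by-arm term, without clustering:

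- SE = SD·√(2(1 − ρ))·√(2/1200) = 2 × 1.265 × 0.0408 = 0.1033
- Power = Φ(0.30·(10 − k)/10 / SE − 1.96)

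| k | Power if kept | Power if dropped |
|---|---|---|
| 0 | 0.83 | 0.83 |
| 1 | 0.74 | 0.81 |
| 2 | 0.64 | 0.78 |
| 3 | 0.53 | 0.75 |

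The last column uses 1200·(10 − k)/10 intervention patients and the full 0.30. It loses less power but is no longer the randomised comparison. Over the stated SD range, keeping two lost clinics moves power from above 0.999 to 0.996 (SD 1) and from 0.49 to 0.34 (SD 3). Clustering would lower all of these.

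The formula gives 0.677 for BZD dose, against the 0.678 stated in Section 6.4.3. It does not reproduce the 0.865 in Section 6.4.1 at SD 3 (it gives 0.491). That is a separate matter, and the power values here show only the relative cost of dilution.

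**The case against.** The strongest reply is that the protocol already protects the comparison. It names intention-to-treat, includes all patients who meet the criteria, and takes outcomes from the EHR without needing clinic cooperation (Section 8), so data keep flowing when a clinic stops taking part. This largely stands: a reader might infer that departed clinics will be excluded and the results biased towards the toolkit, but no passage says so and the general rules point the other way. It fails only for clinics that leave before any activity, whose patients lack an index date.

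Second, a reader might infer that consent is taken after allocation. The protocol does not say that. Sections 9 and 10 describe invitation, meeting and signature as recruitment, and signing first is a natural reading. What stands against the plan is only that the order is left open.

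Third, the one-sided wording of Section 4.3 may simply reflect that only intervention clinics have ongoing work to stop. That is fair, but the sentence still leaves unsaid what happens to the data.

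Fourth, early consent cannot stop a clinic leaving an open trial, and the handling of withdrawn clusters can be left to a statistical analysis plan, which is not at hand. Both are true. The order of consent and randomisation, however, is trial conduct, and no later analysis document can restore it.

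**Conclusion.** The point holds as a gap in design wording, with a cheap remedy. The protocol permits exit from one arm after allocation is known, and its index-date rule leaves some of the resulting patients outside an analysis it calls intention-to-treat.

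It is not a demonstrated bias. The type I error range of 0.057 to 0.140 applies only if lost clinics are dropped, and rests on assumed losses of one to three clinics averaging 1 to 1.5 between-clinic SDs below their arm. With one clinic lost at 1 SD the inflation is trivial. If the clinics are kept as allocated, this mechanism does not inflate type I error. The cost is then power, for example 0.83 to 0.64 with two clinics lost at SD 2, ignoring clustering.

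**What to change.** - **Section 4.2(1):** admit to the randomisation list only clinics whose study champion has already signed the planned consent form, accepting assignment to either arm and use of the clinic's EHR data. Align Section 10 and the synopsis.
- **Section 4.3:** state one withdrawal rule for both arms. Withdrawal ends study activities only, and all 20 randomised clinics are analysed as allocated from EHR data. Report withdrawals by arm.
- **Section 6.3:** give intervention-clinic patients an index date that does not depend on receiving the intervention, for example the same visit-based rule in both arms. The control rule currently refers to intervention visits, so it would need to stand on its own. Without this change, the promise in Section 4.3 cannot be carried out.

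The cost is protocol wording and an earlier signature on a form already planned, with no extra staff or clinics. A few interested clinics may decline before randomisation, which is preferable to losing them afterwards. Including patients who never received the intervention dilutes the effect, as any intention-to-treat estimate accepts.

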### **6.4.3 Milligram equivalent exposure to BZDs**

Effect of various interventions on milligram diazepam equivalent per day exposure to BZDs has shown mean reductions ranging from 25% to 85%. If clinics are randomly assigned to a treatment group and a control group, with an equal number of patients in both groups, a GEE model with a total sample size of 3000 patients, each measured two times before and after intervention, will have statistical power in the range of 0.678-0.969 to detect differences in means of 0.25 or higher in milligram equivalent exposure when the standard deviation is below 2. Pre-period measurements will include the 12-month period prior to index, and post-period measurements will include the 12 months following index. This assumes that the baseline correlation between observations is 0.2 or higher and that we will observe a 20% attrition rate. Power increases for larger mean difference values and drops significantly at higher standard deviation values.

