## 9 RECRUITMENT STRATEGY

Clinics will be identified from patient data pulled from UNC HealthCare's EHR (Epic). Clinic recruitment will be facilitated by [name]. [name], with other team members from the UNC Medical School, will reach out to key stakeholders in the targeted clinics (practice managers &/or physicians). They will provide each clinic with a letter of invitation to participate in the study and will meet with the key stakeholders in person to discuss any questions they have about the nature of the study, procedures, risks, and benefits. A copy of the study's IRB application will also be provided to these stakeholders if requested.

No patient recruitment for participation in the study (except for focus group participants) will be warranted since the study's intervention will be focused on educating providers on improving their delivery of the standard of care.

Provider focus group participants will be identified by the research team and recruited from intervention clinics. They will be sent letters of recruitment and will be contacted in person by [name] or other members of the research team.

Patient focus group participants will be identified by Epic data and recruited from intervention clinics. They will be sent letters of recruitment from the research team.

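### Simple 10:10 randomisation of 20 mixed clinics is valid but likely to leave at least one of clinic type, size or baseline prescribing unbalanced; stratified or constrained allocation would prevent this cheaply

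*Protocol*

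**What the plan says.** Section 4.2(1) gives the whole allocation procedure. A member of the study team "will use the random number generator built into SAS to randomize 10 clinics into treatment and 10 clinics into control groups". If more than 20 clinics are eligible, "20 clinics will be chosen at random, and this list will subsequently be divided into 10 random treatment clinics and 10 random controls". The number per arm is therefore fixed, but nothing else about the clinics enters the draw.

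Section 3.1.3 describes the clusters as "primary care outpatient clinics within the UNC HealthCare System, including family medicine, primary care, and geriatric clinics". Section 3.3 adds, of the health system's clinics in general, that "The patient population served varies across clinics and geographical areas". Section 3.2 plans for 20 clinics and 3,000 patients, or 150 per clinic on average; neither the spread of clinic sizes nor the number of each type is given.

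Three other places bear on the point. Section 9 says that clinics are found from Epic patient data, so some EHR information on them exists before allocation. Sections 6.4.2 and 6.4.3 compute power "with an equal number of patients in both groups". Section 6.3 sets out a pre-post model (Eq. 1) with a group term, a period term, their interaction and an unnamed covariate vector, and Section 6.6 presents the pre-post design as a control of bias.

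**The concern.** Ten clusters per arm are too few for one random draw to be relied on for comparable arms. The protocol itself names a visible source of difference, clinic type, and clinics also differ in size and in how much opioid and benzodiazepine they prescribe. If geriatric clinics, or heavy-prescribing clinics, fall mainly in one arm, the treatment contrast carries differences between clinics that have nothing to do with the toolkit. The estimate becomes less precise and its face validity suffers.

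The timing matters too. An analysis plan can adjust afterwards, but it cannot rebalance clinics that are already allocated, and 20 clusters support only a few clinic-level covariates. Section 6.7 also relies on randomisation to balance missing data between arms, which with 20 units holds on average and not dependably in a single draw.

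**Working it through.** The protocol states no figure for balance, so there is none to reproduce. The inputs are 20 clinics split 10:10 (Section 4.2) and 3,000 patients (Section 3.2). The number of clinics of one type and the spread of clinic sizes are assumptions, shown as ranges.

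**1. Any continuous clinic-level factor.** In units of the between-clinic SD, the difference between two arm means of 10 clinics has SD √(1/10 + 1/10) = √0.2 = 0.447. By the normal approximation:

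- P(difference > 0.5 SD) = 2[1 − Φ(0.5/0.447)] = 26%
- P(difference > 1 SD) = 2[1 − Φ(1/0.447)] = 2.5%

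**2. Clinic type.** There are C(20,10) = 184,756 possible splits. With K clinics of one type (assumed), the hypergeometric distribution gives:

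- K = 3, all in one arm: 2 × C(17,10)/184,756 = 2 × 19,448/184,756 = 21%
- K = 4, 3:1 or worse: 1 − C(4,2)·C(16,8)/184,756 = 1 − 6 × 12,870/184,756 = 58%
- K = 4, all in one arm: 2 × C(16,10)/184,756 = 2 × 8,008/184,756 = 8.7%
- K = 5, 4:1 or worse: 30%
- K = 6, 4:2 or worse: 1 − C(6,3)·C(14,7)/184,756 = 1 − 20 × 3,432/184,756 = 63%

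**3. At least one of the three.** Count as unbalanced a type split as listed above (the 4:0 line is only for scale), or a difference above 0.5 SD in size or in baseline prescribing. Treat the three factors as independent. When the SD is estimated from the 20 clinics themselves, simulation gives about 27.5% for each continuous factor, a little above the 26% in step 1. Then P(at least one) ≈ 1 − (1 − P_type)(1 − 0.275)²:

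| K of one type (assumed) | P_type | At least one of three |
|---|---|---|
| 3 | 0.211 | 59% |
| 4 | 0.582 | 78% |
| 5 | 0.303 | 63% |
| 6 | 0.628 | 81% |

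Direct simulation for K = 3, 4 and 6 gives 58.7%, 78.0% and 80.7%.

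**4. Unequal patient totals and power.** Assume a clinic-size CV of 0.6, that is, an SD of 0.6 × 150 = 90 patients. The arm total then has SD √5 × 90 = 201, and its 95% range is 1,500 ± 1.96 × 201, or 1,106 to 1,894.

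The lowest power in Section 6.4.3 is 0.678. It reproduces as 0.677 with 2,400 patients after 20% attrition, a difference of 0.25, SD 2, correlation 0.2 and a change-score SD of 2 × √(2 × 0.8) = 2.53: Φ(0.25/(2.53 × √(2/1,200)) − 1.96) = Φ(0.46).

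If one arm holds a share p of the patients, efficiency relative to an equal split is 4p(1 − p).

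- On average: 1 − 4 × (201/3,000)² = 0.982, so power is Φ(2.422 × √0.982 − 1.96) = 0.670.
- At 1,106 v 1,894: 4 × 0.369 × 0.631 = 0.931, so power is Φ(2.422 × √0.931 − 1.96) = 0.647.

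Here 2.422 is the standardised effect that corresponds to power 0.678.

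**5. What the model absorbs.** In Eq. 1 the treatment effect is the group-by-period interaction. With an identity link, a constant difference in baseline dose between arms goes into the group term and drops out of that interaction. A time trend or taper response that differs by clinic type does not drop out.

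Section 6.3 specifies this model for milligram-equivalent exposure. Section 5 defines discontinuation as no prescription on days 181 to 360 after index, in patients who qualify by already taking the drug for more than 6 weeks. The power paragraphs for discontinuation speak of two measurements and a small baseline probability, but the definition supplies no pre-index value that could be differenced out.

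**6. The alternative.** With four clinics of one type and two standardised continuous factors, all 184,756 splits were enumerated for 20 simulated sets of clinics. Under the planned method, 78% had at least one imbalance as defined in step 3. Among the best-balanced 10%, about 18,000 splits, none had.

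**The case against.** The strongest answer is that nothing in Section 4.2(1) is wrong. Simple randomisation is unbiased in expectation, and the allocation is already restricted to 10 clinics per arm, so only the covariates are left free. That stands. A reader might infer that the allocation is defective or the comparison invalid; the protocol does not support that.

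A reader might also infer that an uneven baseline dose feeds straight into the dose result. Eq. 1 largely prevents this, and its covariate vector could hold clinic type or size, with the naming reasonably left to an analysis plan. This stands for additive differences in dose. It does not cover differential trends or discontinuation.

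The range of 1,106 to 1,894 patients may suggest a serious loss of power. Converted, it is under one percentage point on average and about three at the extreme.

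The probabilities depend on assumed counts of clinic types and on a chosen threshold of 0.5 SD. Most of the 58% for four clinics is a 3:1 split, the smallest possible departure from 2:2. The protocol gives no link between clinic type and response to the toolkit, so the size of any resulting bias is unknown. All this stands, and it limits the claim to the chance of imbalance.

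Finally, the sentence on varying populations concerns the health system's clinics in general and not the 20 trial clinics. Mean MME and DME per clinic are not ready to hand either, because Section 5 defines them relative to an index date that Section 6.3 places after the intervention starts. Clinic type and eligible-patient counts are easier to obtain.

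**Conclusion.** The point holds as a design improvement. The planned allocation is valid in expectation, but it leaves a chance of about 59% to 81% that at least one of clinic type, size and baseline prescribing is materially unbalanced. That range assumes 3 to 6 clinics of one type, independence of the three factors and the thresholds stated above. The 26% for any single continuous factor needs only the normal approximation.

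It would go too far to say that all three are likely to be unbalanced together, or that extreme imbalance on a given factor is likely: all four clinics of a type fall in one arm with probability 8.7%, and a difference above 1 SD has probability 2.5%.

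The consequence is weaker comparability and precision, most of all for discontinuation; for dose, what remains is any trend or taper response that differs by clinic type. Loss of power from unequal arm totals is minor: from 0.678 to about 0.67 on average and 0.65 at the extreme, at a clinic-size CV of 0.6 and on the protocol's own patient-level basis.

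**What to change.** Before allocation, extract for each of the 20 clinics its type, its number of eligible patients and, where feasible, mean MME and DME over a fixed calendar window that does not depend on patient index dates. Then either stratify on clinic type and size, or draw the allocation at random from a pre-specified well-balanced subset of the 184,756 possible splits, for instance the best-balanced 10%. State the rule in Section 4.2(1), and adjust for the few balancing variables in the outcome models.

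The cost is a short data pull with dose conversion for the baseline means, a short SAS program, one paragraph of text, and carrying the balancing variables into the analysis. No further clinics or patients are needed. The change must be made before clinics are allocated.
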